## Abstract

**Background::**

Social Prescribing (SP) is an intervention to link users of the primary healthcare services to non-clinical organizations based on the community to tackle social determinants of health. Despite the potential benefits of SP, the effectiveness of this complex intervention remains uncertain. This paper presents the study protocol of the evaluation of the first SP project in Portugal.

**Methods::**

A mixed-methods study will be conducted to evaluate the SP project. For the quantitative component, a longitudinal, prospective study with a pre-post design will be performed. Data on patients referred to SP will be collected in four different points in time throughout the intervention, using questionnaires on patients’ health status and sociodemographic characteristics, and scales on patients’ well-being, quality of life and activation. The secondary data will be collected using patients’ medical records and SP’s forms about the referral and social responses elaborated within the intervention. Semi-structured interviews with patients and focus groups with stakeholders will be conducted to assess experiences of participation and improvement suggestions on SP.

**Conclusion::**

Comprehensive and complementary evidence will provide insights and learning for the implementation of future SP interventions. This can contribute to inform policy and practice, and to increase investment in social prescribing interventions.

## Background

The health of individuals is broadly acknowledged to be influenced by a combination of multilevel interrelated determinants – genetic, psychological, lifestyles, ecosystems, as well as social, economic, cultural and structural (including healthcare system) [1]. These multiple complex factors, along with daily life contexts, frequently translate into health inequities [1].

It has been evidenced that situations of loss of employment, poor social and economic resources, social isolation, interpersonal problems, or illness of a relative can trigger the manifestation of physical symptoms, stress, depression, anxiety [2]. Moreover, situations of social exclusion and economic disadvantage are associated with low levels of health literacy, less means for healthy lifestyle habits and decreased access to healthcare, that can lead to non-communicable diseases, and, consequently, to higher mortality and lower life expectancy [3,4,5]. In these cases, an exclusively clinical approach may not be the most appropriate response [2,6].

Social Prescribing (SP) has a potential role in effectively tackling social determinants of health and in preventing exacerbation of pre-existing diseases, with the purpose of improving users’ health and well-being [6,7]. SP is a complex intervention and a solution to respond to non-clinical needs of individuals and to articulate healthcare with other sectors of society [6]. This intervention has been considered an innovative public health approach that allows the provision of integrated care by linking healthcare services to the tertiary sector, and thus providing more than solely traditional health care [8,9]. Furthermore, SP can contribute to reduce inequities by covering and addressing the needs of vulnerable populations (such as migrants, individuals with mental illness, or at risk of social isolation) [10,11,12].

The process of SP starts with the identification of a patients with social, emotional or practical needs by a health professional. These patients include people with one or more chronical medical conditions, who have complex social needs which affect their health and well-being, who are lonely or isolated, or who need support related to mental health [10]. The health professional refers the patient to a link worker, who is responsible for, in a SP appointment, assessing the patient’s needs in detail and developing a tailored plan of activities in collaboration with the patient [13]. The link worker is a key professional in the SP process and provides personalised support to individuals, connecting people to community groups and statutory services [10]. Some of the link worker skills are ability to listen, ability to support people in a way that inspires trust and confidence, ability to communicate effectively with all stakeholders, and commitment to collaboratively working with all local agencies [10]. The link worker helps patients and their carers to navigate the voluntary and community services [8].

Based on the identified needs and the co-designed plan, the patient may be referred to a diverse set of social responses from the community resources, such as physical activities, dance groups, arts and crafts, professional training, education activities, food bank support, day-care centre, volunteering, among others. These responses can be provided by different institutions, including local authorities, social services, community and voluntary organizations [10].

SP has been broadly implemented in the English National Health Service (NHS) as an intervention of the NHS Long-Term Plan since 2019 [10,14]. One of the few randomized clinical trials conducted to evaluate SP has showed improvements in anxiety, pain and self-rated overall health, although no significant changes in depression levels. Higher prescription of medications and higher costs were also found in the intervention group [15]. Another study conducted in the United Kingdom evidenced an increase of self-reported physical activity, a better self-perception of quality of life, well-being and lower BMI in patients enrolled in SP activities. Nevertheless, the authors did not found differences in frequency of alcohol consumption and smoking status among these patients [16]. Other studies also seem to indicate that SP has the potential to promote empowerment and activation for health, in terms of increased knowledge, confidence, motivation and ability of the users to self-manage their health [17,18].

The available research does not provide consistent evidence on the impact of SP. Several studies do not present significative differences in anxiety, depression and well-being levels between control groups and groups of patients enrolled in SP [11,19]. Furthermore, a lack of significative differences in SP’s impact between baseline and follow-up evaluation moments has also been evidenced [20]. The main limitations presented in these studies are small sample sizes, no use of inferential statistics and low response rates to the evaluation instruments, which compromises the quality of the evidence provided [11].

Evidence on the provision of integrated care and networking in SP interventions is scarce, although some policy reports suggest that SP may reinforce the proximity between the social and healthcare sectors by having the participation of local organizations in SP as key-partners in the implementation of personalized, local and preventive activity plans for the patients [10]. Other publications report that SP can also increase the patients’ sense of belonging to the community, in addition to fostering a more efficient local economy [6,11].

In terms of the health system, although contradictory results are often found, some studies indicate that SP can have an impact in the reduction of the number of appointments with a General Practitioner (GP) and in decreased prescription of antidepressant, hypnotic, and anxiolytic medicines for patients enrolled in this type of intervention [10,21]. Other research shows a greater workload of professionals involved in SP and higher costs of referral to this intervention [11].

SP evaluation studies are still incipient and present controversial results. When it comes to the evaluation of SP, a variety of studies has been performed, comprising randomized controlled trials, case-control studies, case studies, qualitative studies, among others, that used various data collection instruments applied with different periodicities, and measured different outcomes [19,20,22,23,24,25]. Indeed, although the wider health benefits of the SP intervention, such as improve patients’ health, well-being and quality of life, should be covered, other outcome measures can be added according to the specific objectives of each intervention [10,20]. Thus, this heterogeneity poses a great challenge when designing SP evaluation studies [20,26,27]. In addition, since SP is a complex intervention, evaluation studies that give insights on its impact for the patients, for the health system and for the community would be valuable [10].

### SP in Portugal

The first SP project in Portugal was launched in two Primary Healthcare Units – *Baixa and Almirante Family Health Units –* located in central Lisbon and provide healthcare to approximately 27500 patients with a high variability of sociodemographic characteristics. All users registered in these Primary Healthcare Units can be referenced to SP, except patients with severe and uncontrolled mental health issue.

The intervention starts when a healthcare professional (general practitioner, nurse or psychologist), during an appointment with a patient, identifies social needs, namely related to social isolation, migrant integration, mental health, physical activity, employment and training, or housing issues. After that, the healthcare professional makes an internal referral through an SP online platform to the link worker, which in the Portuguese context is the unit’s social worker. In this platform the healthcare professional fills in the reasons for referral, presence of chronic diseases and brief history of the patient. Afterwards, the patient is encouraged to schedule a SP appointment with the social worker to continue the support of SP.

In the SP appointment, the social worker performs a needs assessment and helps patients to identify the issues that impact on their health and well-being. Then, the social worker develops a tailored intervention plan in collaboration with the patient, based on the person’s priorities, interests, values and motivations [10]. This plan foresees an external response provided by community partners from the health unit’s geographical area or according to the patient’s preference.

In the next stage of the SP pathway, the social worker refers the patient to the key community partners. Communication between the social worker and community partners is made by e-mail containing information about the patient’s needs and the social partner’s availability of response, and through online forms to monitor the activities in which the patient is participating and the frequency of adherence.

Throughout SP intervention, the social worker communicates with the patient through face-to-face SP appointments or phone calls to follow the compliance and satisfaction with the activity plan, and communicates with the healthcare professional to give feedback on the patient´s case. The number of appointments with the link worker depends on each user’s needs, but as documented elsewhere, the SP intervention takes around 4–6 appointments per patient [16,28], although, if necessary, more follow-ups can be scheduled. The average length of the appointments is 30 minutes.

Overall, the SP intervention changed the conventional role of the social worker in Health Units in Portugal. Health professionals usually referred patients to the social work service when the issues were mainly associated with administrative issues in access to social and health benefits, such as support to buy medicines, functional dependency or end of life support. SP intervention allowed to expand the role of the social worker within primary care to include: advice and support on lifestyle changes (physical activities, food habits), community engagement, employment and training, mental health promotion, personalised emotional and social support, as well as connect people to community groups and statutory services.

## Research aims

The aim of this protocol is to evaluate the SP intervention implemented in Primary Healthcare Units of Lisbon, with a focus on patients’, health-social sector collaboration, and health system’ levels.

The specific objectives are to: I) Explore the extent to which the SP intervention leads to enhance patients’ quality of life, well-being, and activation; II) Explore experiences of patients during their participation on SP activities, including positive and negative aspects, and suggestions for improvement; III) Understand the implementation of SP from the perspectives of health professionals, social workers, and community partners; IV) Describe the networking experience of the key actors involved in SP.

## Methods

### Study design

This evaluation protocol will use a mixed-methods approach consisting of four studies, each one addressing a specific objective, as illustrated in ***Figure 1***.

**Figure 1 F1:**
[figure not shown]
Description of the studies and objectives.

#### Study 1 – Evaluating the quality of life, well-being and activation of patients in SP over time

##### Design and participants

In order to explore the extent to which the SP intervention leads to enhance patients’ quality of life, well-being and activation, a pilot study will be conducted, with an exploratory, longitudinal and prospective design, comprising four assessment moments: baseline, follow-up 1 (third month), follow-up 2 (sixth month) and follow-up 3 (twelfth month) (***Figure 2***).

**Figure 2 F2:**
[figure not shown]
Moments of assessment.

The sample will include all the patients referred for the first time to a SP appointment who fulfil the inclusion criteria: being ≥18 years old and living in Lisbon. Patients who are terminally ill, who present severe and uncontrolled mental health issues (e.g. uncontrolled schizophrenia, acute psychosis), who are housebound, and who present uncontrolled use of drugs and/or alcohol are excluded from participation in the study. A recruitment target is estimated at 300 patients, with the chances of non-acceptance of participation and losses to follow-up (attrition rate) being estimated at >20%, based on previous studies [15,19,20,28].

All patients referred to SP in the first 12 months will be included in the baseline and the data collection will be conducted during 24 months. Both the patients who undertake SP activities and those who end their participation during data collection period will be included in the follow-ups.

##### Data collection

Before the first SP appointment, the patient will be invited to participate in the study (baseline) and will be asked to provide a written informed consent. ***Table 1*** summarizes the instruments and measures used for data collection throughout the assessment moments.

**Table 1 T1:** Summary table of the evaluation’s quantitative component.

EVALUATION MOMENT	INFORMATION SOURCES	INSTRUMENTS	GROUPS OF VARIABLES	VARIABLES

***Baseline, follow-up* 1, 2 and 3**	Patient	Questionnaire	Sociodemographic characteristics	– Sex – Age – Country of birth – Educational level – Employment status – Number of people in the household – Average monthly income of the household – Preferred Language

			Health status	– Weight and height – Physical activity – Smoking status – Alcohol consumption

			Well-being	– WEMWBS

			Patient’s activation	– PAM13

			Quality of life	– EQ-5D-3L

	Computer system	Health units’ Databases	Health status	– Number of chronic diseases – Types of chronic diseases – Medications consumption

			Use of healthcare services	– Number of appointments in the Primary Healthcare Services – Number of hospital admissions – Number of emergency episodes

***Follow-up* 1, 2 and 3**	Health professionals, social workers and community partners	Forms	Characterization of the intervention	– Type of health professional that made the referral – Motive for referral – Activities provided – Accepted and planned activities – Adherence to the activities

A questionnaire will be applied to collect data on: I) Sociodemographic characteristics (sex, age, country of birth, educational level, employment status, number of people in the household, average monthly income of the household and preferred language); II) Health status (height and weight, physical activity, smoking behaviour, and alcohol consumption); III) Mental well-being (using the Warwick-Edinburgh Mental Well-being Scale – WEMWBS); IV) Patient activation (through 13-item patient activation measure – PAM13); and V) Quality of life (using the EuroQol 5 dimensions instrument – EQ-5D-3L). Prior authorization for the use of each of the scales in Portuguese and English versions was obtained.

The questionnaire was tested in a purposive sample of patients not enrolled in the study. As a result, the guidelines for filling the questionnaire were simplified in order to ensure clarity of the information.

In addition to the questionnaire, secondary data will be collected from patients’ medical records. This data will consist of indicators related to the use of healthcare services (number of appointments in the Primary Healthcare Units, of hospital admissions, and of emergency episodes) and health status (number and types of chronic diseases, and medications consumption).

In the follow-ups, data will be collected using the same instruments of baseline. The questionnaire will be applied in the health unit before the SP appointments. In order to ensure the inclusion of people with low literacy and educational levels or that experience difficulties with self-administration, the questionnaire will be administered by a researcher through an interview (either in Portuguese or in English). In situations where the patient has interest in participating in the study but is unable to communicate in Portuguese or English, or has learning disabilities and other types of disabilities, a person that accompanies the patient can help in collecting the information, with the consent of the patient and when applicable. A unique alphanumeric code will be used to identify each participant in all evaluation instruments throughout the longitudinal assessment moments.

Additional information about the SP intervention will comprise data on the type of health professional that made the referral and motive for signposting (from the SP form filled in by the health professional) and information about the SP activities provided, accepted and programmed, and patient’s adherence to the activities (through the online forms filled in by the community partners).

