The SP’s impact on the collaboration between the health and social sectors will also be evaluated. Specifically, SP interventions and social responses provided to patients, and accepted and performed by them will be assessed using information from the quantitative, longitudinal study. The focus groups will provide information on articulation and communication between both sectors. Additionally, it will provide an insight into the health professionals’, social workers’ and community partners’ perspectives, which has only been obtained in few studies and remains an important gap in the literature regarding SP evaluation [19,20].

More broadly, the collection of information about the use of healthcare services will enable an evaluation of the influence of SP at the health system level. The relevance of assessing SP’s effects on this dimension has been previously highlighted [21,24]. SP responds to social needs that often lead patients to seek solutions in healthcare services. Thus, by providing effective responses to these needs, SP can contribute to reduce the overuse of healthcare services and the health professionals’ workload.

Besides the SP’s impact, this evaluation study also intends to provide useful knowledge on its process of implementation. The follow-up of all patients referred to SP, including those who conclude or withdraw their participation from SP activities before the follow-up evaluations represents an important innovation of this study. This will shed light on barriers to adherence to SP’s activities, while also allowing a comparison of outcomes between adherent and non-adherent patients.

Another differential of this evaluation study is that information on activities provided by community partners, accepted by patients and performed within SP will be collected and monitored for each participant. This will allow to collect detailed information about each patient’s pathway within SP, which has been described as a limitation in several studies [11,17]. It is acknowledged that the use of this approach is crucial to understand both the scope and the acceptability of the intervention among patients [34].

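### As worded, the primary-care appointment count takes in the social prescribing appointments themselves, which adds to the use that the intervention is expected to reduce

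*Protocol article*

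**What the plan says.** All references are to the protocol article.

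- **Outcome.** Study 1, Data collection, takes from medical records the "number of appointments in the Primary Healthcare Units, of hospital admissions, and of emergency episodes". Table 1 words the first item as "Number of appointments in the Primary Healthcare Services" and lists it at baseline and at all three follow-ups. Neither place says which professionals' appointments count.
- **Who delivers SP.** Under SP in Portugal, the patient is referred "to the link worker, which in the Portuguese context is the unit’s social worker". The referral is made during an appointment with a general practitioner, nurse or psychologist.
- **Where.** For the follow-ups, Data collection states: "The questionnaire will be applied in the health unit before the SP appointments". This implies that the SP appointments also take place in the unit.
- **How many.** Citing other work, the article says that "the SP intervention takes around 4–6 appointments per patient", depending on need and with more if necessary.
- **When.** Baseline is taken before the first SP appointment, so no SP appointment can fall in the baseline count.
- **Use of the result.** Data analysis classes healthcare use as secondary and plans comparisons of baseline with each follow-up by GEE. The Discussion says that the healthcare-use data will allow SP's influence at health-system level to be evaluated, and expects that "SP can contribute to reduce the overuse of healthcare services and the health professionals’ workload". It also acknowledges that Study 1 has no control group.

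**The concern.** The outcome is defined by where the appointment happens, and the intervention consists partly of appointments in that same place. An extraction that follows the wording would find no SP appointments before baseline and several per patient afterwards. That difference arises whether or not patients change how they use general practitioners, nurses or psychologists.

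A concurrent control group would not remove such a component, but it would show what other use does without SP. An uncontrolled pre-post comparison offers no such check, so the added visits go straight into the estimated change.

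The health system is one of the three levels named in the Research aims and again in the Discussion. If the count is taken literally, a real fall in clinical consultations could be reported as a rise.

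Subtracting the SP appointments afterwards is not provided for. Table 1's intervention data cover the referring professional, the motive, and the activities offered, accepted and adhered to, but not the number of SP appointments. Under Ethical considerations, the unit's professional extracts and anonymises the records before the research team receives them, so the appointment type has to be requested at extraction.

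**Working it through.** The plan gives no baseline appointment rate, expected reduction or other figure for this outcome, so there is no stated result to reproduce.

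**Inputs**
- S, SP appointments per patient: 4 to 6 (SP in Portugal, taken there from other studies).
- B, other primary-care appointments per year before SP: assumed at 4, 6, 12 and 20.
- r, true proportional reduction in those appointments: assumed at 0 to 50%.
- Equal 12-month periods before and after, with all SP appointments inside the later one. This is assumed so that only the effect of the definition is shown.

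**Formula**
Measured count after = B × (1 − r) + S. Measured ratio = [B × (1 − r) + S] / B. The true ratio is 1 − r.

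**No true change (r = 0).** The apparent increase is S / B:
- B = 4: 4/4 to 6/4, an increase of 100% to 150%
- B = 6: 4/6 to 6/6, an increase of 67% to 100%
- B = 12: 4/12 to 6/12, an increase of 33% to 50%

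**True 30% reduction (true ratio 0.70)**
- B = 6: 6 × 0.7 = 4.2; 4.2 + 4 = 8.2 and 4.2 + 6 = 10.2; ratios 8.2/6 = 1.37 and 10.2/6 = 1.70
- B = 12: 12 × 0.7 = 8.4; 12.4 and 14.4; ratios 1.03 and 1.20
- B = 20: 20 × 0.7 = 14; 18 and 20; ratios 0.90 and 1.00

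**When the sign reverses.** The ratio exceeds 1 when S > r × B, that is, when B < S / r:

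| True reduction r | Break-even B, S = 4 | Break-even B, S = 6 |
|---|---|---|
| 10% | 40 | 60 |
| 20% | 20 | 30 |
| 30% | 13.3 | 20 |
| 50% | 8 | 12 |

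Below the break-even rate, a real reduction is measured as an increase. Above it, the reduction is understated but keeps its sign.

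**Index consultation.** Because referral happens during an appointment, any look-back that reaches that visit contains at least one consultation by design. This raises the baseline count and pushes the other way, so the net bias is hard to predict.

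**After the change.** With SP appointments left out, S = 0 and the ratio under the same equal periods is the true one: 1.00 with no change, 0.70 with a 30% reduction.

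**The case against.** The strongest reply is that the article never says SP appointments are counted. It uses SP appointment as a term of its own and lists health professionals separately from social workers. It cites literature on general practitioner appointments, and the workload it hopes to reduce is that of health professionals. The authors may well intend a narrower count. This stands as a limit: inclusion is the literal reading, not an express statement. The outcome wording still does not carry the narrower meaning, and whoever extracts the data will work from that wording.

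The figure of 4 to 6 is borrowed, varies with need, and sits beside follow-up by phone, so the number of recorded visits may differ. This also stands.

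Social-worker appointments are real work for the unit, so a total that includes them is a legitimate measure. That is right, and it is met by reporting both counts.

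Three stronger readings are tempting but not supported:
- **Windows of unequal length.** Assessments at 3, 6 and 12 months are unevenly spaced, and a reader might infer that counts over unequal periods will be compared without a person-time adjustment. The article states no counting window, a fixed look-back at each assessment would be equal, and an article may leave this and the count model to the full plan.
- **Certain reversal.** The example with 20 visits a year shows that it is not certain.
- **All healthcare-use measures affected.** SP appointments do not enter hospital admissions or emergency episodes.

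**Conclusion.** The point holds for primary-care appointments only. As worded, the outcome covers the intervention's own appointments, all of them after baseline, and nothing in the article removes them. The Discussion nevertheless attaches a health-system conclusion to these data.

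With 4 to 6 SP appointments and a true 30% reduction, the measured ratio would be 1.37 to 1.70 at an assumed 6 other visits a year, and 0.90 to 1.00 at an assumed 20, against a true 0.70. The direction of this component is certain if the appointments are counted. Its size, and whether it reverses the result, depend on assumed baseline use and on a number of SP appointments taken from elsewhere.

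Severity is moderate to low. Healthcare use is a secondary outcome of an exploratory pilot, it appears in none of the four specific objectives, and the authors already advise caution because there is no control group. It still deserves correction, because the change is easy before extraction and harder afterwards.

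**What to change.** Before records are extracted:

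1. Define the outcome as appointments with a general practitioner, nurse or psychologist in the unit. Exclude SP and other social-worker appointments, and exclude the consultation at which the referral was made.
2. Extract the number of SP appointments per patient as a separate variable, add it to the intervention data in Table 1, and report it as intervention dose.
3. Also report the total including SP appointments, labelled as a measure of unit workload, so that the reader sees both quantities.
4. Use the same definition in Data collection and in Table 1, which now name the place differently.

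The cost is a slightly more detailed extraction, by type of professional, from the unit databases already planned as the source. No new patient contact, visit or questionnaire is needed. The definitions of hospital admissions and emergency episodes need no change on this account.

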##### Data analysis

The primary outcome measures comprise the levels of quality of life, well-being and the patients’ activation. The sociodemographic characteristics, health status, use of healthcare services and characteristics of the intervention are considered the secondary outcome measures. A statistical analysis will be conducted to analyse the association between primary and secondary outcomes. Furthermore, comparative measures between the baseline and follow-up 1, 2 and 3 will be computed, using generalized estimating equations (GEE) [29]. All analyses will be conducted using the IBM SPSS Statistics software, in the most recent version available.

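### The primary-care appointment count does not exclude social prescribing appointments, which are held in the same unit and only after baseline, so it can hide or reverse a real fall in use

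*Protocol article*

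**What the plan says.** The Study 1 Data collection section states that "secondary data will be collected from patients’ medical records" and lists as indicators of service use the "number of appointments in the Primary Healthcare Units, of hospital admissions, and of emergency episodes". Table 1 gives the first of these as "Number of appointments in the Primary Healthcare Services", to be collected at baseline and at all three follow-ups. Neither wording names a profession, a type of appointment or an exclusion.

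Under Data analysis, "use of healthcare services and characteristics of the intervention are considered the secondary outcome measures". The same section compares baseline with follow-ups 1, 2 and 3 by generalized estimating equations, without saying which outcomes enter the models.

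On the intervention, the section SP in Portugal says that the referral goes "to the link worker, which in the Portuguese context is the unit’s social worker". It adds, citing other studies, that "the SP intervention takes around 4–6 appointments per patient", that more can be scheduled, that the average appointment lasts 30 minutes, and that contact may be in person or by phone. The Data collection section has the questionnaire completed in the health unit ahead of SP appointments, which implies that those appointments take place there.

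The Discussion uses the service-use data to assess the health-system level, with the expectation that "SP can contribute to reduce the overuse of healthcare services and the health professionals’ workload".

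**The concern.** On its plain wording the outcome can contain the intervention. An SP appointment is an appointment, in the primary healthcare unit, with a member of the unit's staff. Participants are referred to SP for the first time and baseline precedes the first SP appointment, so the baseline count holds no SP visits and each follow-up count may hold several. The distortion therefore runs in one direction, towards more apparent use. There is no control group against which an added block of visits would show up.

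The Background motivates this outcome with studies of GP appointments, which is narrower than the variable listed. A rise produced by SP visits could be read as SP increasing demand, or a real fall in clinical visits could go unseen. The intervention variables in Table 1 cover the referrer, the motive, the activities and adherence. They include no number of SP appointments, so the listed variables alone would not allow the visits to be subtracted.

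**Working it through.** **Inputs from the protocol article.** SP appointments per patient: around 4–6, cited from other studies and so not reproducible by calculation. Baseline: before the first SP appointment. Control group: none.

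**Assumptions.** The article gives no baseline visit rate and no expected reduction. I take a baseline of b = 3, 6, 9 or 12 visits per patient in the comparison window, a true fall in non-SP visits of r = 10%, 20% or 30%, windows of equal length, and s SP visits recorded as unit appointments.

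**Formulas.** Observed follow-up count = b × (1 − r) + s. Observed change = observed count / b − 1. The baseline at which the added visits exactly cancel the fall = s / r.

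**Example.** b = 6, r = 0.20, s = 4: 6 × 0.8 + 4 = 8.8, and 8.8 / 6 − 1 = +47%. With s = 6: 4.8 + 6 = 10.8, or +80%.

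**Observed change with s = 4 to 6:**

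| Baseline b | True fall 10% | True fall 20% | True fall 30% |
|---|---|---|---|
| 3 | +123% to +190% | +113% to +180% | +103% to +170% |
| 6 | +57% to +90% | +47% to +80% | +37% to +70% |
| 9 | +34% to +57% | +24% to +47% | +14% to +37% |
| 12 | +23% to +40% | +13% to +30% | +3% to +20% |

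The sign is reversed in every cell.

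**Break-even baseline.** For a 20% fall, 4 / 0.2 = 20 visits to 6 / 0.2 = 30 visits. For a 30% fall, 13.3 to 20 visits. For a 10% fall, 40 to 60 visits.

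**Fewer SP visits in the window** (early follow-up, early leavers, phone contact). With s = 1 to 2 and a true fall of 20%, the observed change is +13% to +47% at b = 3, −3% to +13% at b = 6, −9% to +2% at b = 9, and −12% to −3% at b = 12. At the higher baselines the fall is mostly shrunk rather than reversed.

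**SP visits not recorded as unit appointments.** s = 0, and the observed change equals the true change.

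**The case against.** The strongest reply is that the variable is named in a few words and an article leaves coding rules to the full protocol or the extraction specification. The article usually labels the social worker's visits as SP appointments and uses the unlabelled word for the clinical visit before referral, so an outcome meaning ordinary clinical appointments is a natural reading. Nothing says how SP visits are coded in the unit databases. This part stands: inclusion is a reading of the wording, not an express rule, and the bias is conditional on it. It does not dispose of the point, because the wording followed literally takes in SP visits and no listed variable would correct for them.

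The size is also open to challenge. The figure of 4–6 covers the whole intervention, is tied to no follow-up window, and will be lower for patients who stop SP but stay in follow-up. That stands too, and is why 4–6 is treated as an upper range.

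A reader might infer three stronger things that the documents do not support:

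- **That the plan expressly counts every appointment.** It is silent on inclusion and exclusion.
- **That the workload conclusion fails whether SP visits are counted or left out.** The Discussion speaks of health professionals' workload. Study 3 uses that term for GPs, nurses and psychologists and lists social workers separately. A count without SP visits would fit that statement.
- **That a pooled count could never be separated later.** Under Ethical considerations, unit staff extract the data and hold the link between code and patient. Pooling by profession is not stated, and re-extraction is not ruled out.

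**Conclusion.** The point holds conditionally. As worded, the primary-care appointment count does not keep out the intervention's own visits, which can only add to follow-up. If they are recorded as unit appointments, the before-after comparison is inflated by up to about 4–6 visits per patient over the intervention. Under the assumed baselines of 3–12 visits, that full number reverses a true fall of 10–30%, while one or two visits mask it in part or in full, or reverse it at lower baselines. If they are recorded elsewhere, there is no bias.

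The reach is limited to one component of a secondary outcome in an exploratory, uncontrolled pilot whose authors already ask for cautious interpretation. Quality of life, well-being, activation, hospital admissions and emergency episodes are untouched. It is still worth settling before extraction, because the Discussion relies on service use for its health-system assessment.

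**What to change.** In Table 1 and the Study 1 Data collection text, define the outcome as *number of appointments with GP, nurse and psychologist, by type of professional, at baseline and at each follow-up, excluding SP appointments*, and use that count for the comparison with baseline.

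Extract two further counts:

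- SP appointments, as a measure of intervention dose.
- Non-SP social-work appointments. The section SP in Portugal describes an existing social-work service for benefits and dependency issues. Dropping all social-worker visits would lose that ordinary use before and after baseline.

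In the Discussion, limit the workload statement to GPs, nurses and psychologists, or report SP contact time beside it. On the article's figures, that is 4–6 × 30 minutes = 2–3 hours per patient completing the cited number of appointments.

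The cost is one extra field (professional or appointment type) in an extract already planned, plus the wording changes. No patient contact and no new data source are needed.
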